## Informed Consent

An information sheet is sent to all potentially eligible patients (see additional file 2: Appendix B). Patients are asked to sign and return, with their postal questionnaire, a reply slip (see additional file 2: Appendix B) to allow further contact regarding the research. At their first consultation for baseline data collection, the GP/practice nurse ensures their understanding of the study, allows them the opportunity to ask questions and confirms their willingness to participate in the study before asking them to sign a consent form (see additional file 2: Appendix B).

## Ethical Approval

Ethical approval has been granted by the Ethics Committee of the Irish College of General Practitioners and the Queen's University Research Ethics Committee.

## Data Collection

Data collection will involve three components:

• **Questionnaire **posted to patient from the practice with administrative assistance from the SPHERE research nurse. Questionnaire is posted back to the practice in a pre-paid envelope. The research nurses liaise with practice staff to follow up non-responders.

• **Consultation **data gathered by practice staff and inserted into one page SPHERE study baseline measurement record.

• **Chart search **to establish process of care and collect patient outcomes recorded in GP records. This is carried out by research nurse (after obtaining patient consent), and recorded onto SPHERE study database.

The above data will be collected at three time points:

1) Baseline

2) One year

3) Two years.

Data are collected at one year to assess the initial effects of the intervention. No results of any interim analyses will be revealed to any member of the research team unless the Data Monitoring Committee (see below) determine that it is unethical to continue the study.

Data to be collected are described below.

**Questionnaire components **(see additional file 3: Appendix C)

A. Physical and mental well-being: SF-12.

B. Exercise: Godin Leisure-Time Exercise Questionnaire.

C. Smoking status: adapted from SLÁN study [33].

D. Diet: DINE, including question regarding portions of fresh fruit and vegetables.

E. Personal and demographic variables:

a. Demographics: name, date of birth, marital status, educational level, occupation, GMS eligibility (for practices in the Republic of Ireland).

b. Economic analysis questions: journey time to GP and hospital.

c. Health service attendance in previous 12 months: including hospital outpatient services, admission to hospital as an inpatient, visits to Accident and Emergency department and days spent as inpatient.

F. Adherence to medication: Medication Adherence Report Scale MARS-5.

**Consultation/physical assessment components (taken by practice nurse/GP) **(see additional file 4: Appendix D)

1. Blood pressure.

2. Total serum cholesterol concentration (HDL and LDL).

3. Current medications, dose and contraindications.

4. Height in cm/weight in kg/BMI/waist circumference in cm/waist hip ratio.

**Chart search data (collected by SPHERE research nurse) **(see additional file 4: Appendix D)

1. Cardiac history: months since diagnosed with CHD, record of myocardial infarction and time since myocardial infarction, presence of angina, investigation confirming diagnosis, previous PTCA or CABG, presence of diabetes.

2. Number of GP and practice nurse consultations in last 12 months.

3. Number of attendances at outpatients/inpatient services in last 12 months.

4. Recording of risk factors in medical records: smoking, cholesterol and blood pressure.

## Data Analysis

### Description of study participants

Practices and patients participating in the SPHERE study will be heterogeneous. Participating practices will be described in terms of:

• Number and gender of full time equivalent GPs

• Number of practice nurses

• Numbers of support staff

• Practice list size – in the Republic of Ireland this will be presented as GMS list size and estimated non-GMS list.

Participating patients will be described in terms of:

• Age

• Gender

• Disease duration

• Nature of cardiovascular disease:

Angina

MI

• Procedures:

Angioplasty

CABG

• Socioeconomic status (according to occupation).

### Randomised controlled trial analysis

Primary outcomes include:

• Blood pressure

• Total cholesterol

• Physical and mental status as measured by the SF-12

• Hospital re-admissions.

Secondary outcomes include:

• Measure of the process of care

SPHERE visits

Total number of GP visits

Total number of hospital OPD visits

Recording of risk factors in GP records

• Body Mass Index/Waist-Hip Ratio

• Exercise: Godin Leisure-Time Exercise Questionnaire

• Smoking status

• Diet: DINE, including question regarding portions of fresh fruit and vegetables

• Adherence to medication (Medication Adherence Report Scale MARS-5).

All results are analysed using SPSS and Stata statistical software. Statistical modelling is carried out using Stata statistical software which has a facility for complex survey sample analysis that allows for adjustments in data analysis based on design effects, planned or unplanned. Statistical significance will be taken at the 5% level for both primary and secondary outcomes. The analysis examines intervention vs control groups on study completion, as opposed to looking at changes in the intervention and control groups from baseline.

### Sub-group analyses

Sub-group analyses will be carried out on the following groups:

• Angina only vs other diagnoses

• CABG vs angioplasty

• Diabetes vs non-diabetes

• Men vs women

• Northern Ireland vs Republic of Ireland

• Patients < 70 years vs older.

Analyses will be carried out using two approaches:

• By intention to treat i.e. including all randomised patients, regardless of their participation in the intervention.

• Sensitivity analyses will explore whether adherence to the intervention influences the effect of the intervention on primary outcomes.

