## Sample Size Calculation

The study aims to achieve a final sample of 635 patients from at least 42 practices (see Figure 1).

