**Figure 1 F1:**
[figure not shown]
Flow of Practices and Patients Throughout Trial.

Sample size calculations are based on the following:

• Power of 80% and alpha of 5%.

• Only patients agreeing to participate in the study and completing baseline data collection will be entered into the study. There will, therefore, be 100% uptake at the start of the study. Reasons for non-participation will be documented and recorded, and participation rates will provide a measure of the acceptability of this type of intervention to patients.

• A final completion rate of 70% is anticipated based on similar studies in the West of Ireland 7 (completion rate = 68.7%) and Dublin [28] (completion rate = 93%).

• Practice attrition of 12.5% has been allowed for (though practice attrition in another similar study was only 4% [28]).

• Improvements in the control group as a result of participation in a research study have been anticipated [25].

• Design effects are calculated using intracluster correlation coefficients from data from similar populations in Galway and Scotland ([name], personal communication).

A total sample size of 907 patients recruited from 46 practices gives a varying but minimum power of 80% to detect significant changes in proportions with poor blood pressure and cholesterol control, physical and mental well being (SF-12) and hospital readmissions at two years. (Detailed power calculations are given below). This allows for a final patient follow-up and retention rate of 70% and a practice attrition rate of 10%. The number of practices is rounded up from 46 to 48, to allow equal numbers of practices to be recruited in each of the three study centres. Sixteen practices will therefore be recruited in each of the three centres, eight intervention practices and eight control practices. Twenty patients are recruited in each practice. Final data analysis will incorporate modelling techniques that are more statistically efficient and will ensure greater power to detect significant changes in study outcomes.

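### The age subgroup is cut at 70 with no stated reason although date of birth is collected; testing effect modification by that split probably loses a quarter to two fifths of the age information, depending on the age distribution

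*Protocol article*

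**What the plan says.** Under Sub-group analyses, the protocol article states: "Sub-group analyses will be carried out on the following groups". Six contrasts follow. Five are categories by nature: diagnosis, procedure, diabetes, sex and jurisdiction. The sixth is "Patients < 70 years vs older".

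Exact age can be derived. Under Data Collection, the questionnaire components include "Demographics: name, date of birth, marital status", and Description of study participants lists age among the patient characteristics to be reported.

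The article gives no reason for choosing 70. The eligibility criteria, the treatment targets and the stratification of randomisation (by practitioner whole-time equivalents) attach no meaning to that age. It also gives no mean, spread or share under 70 for the expected patients, and no power for any subgroup contrast.

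**The concern.** A two-group cut treats a patient of 50 and one of 69 as alike, and patients of 69 and 71 as different. If the intervention works progressively better or worse with age, much of the evidence for that lies in the spread of ages within each group, and the split does not use it.

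At stake is the chance of seeing a real age trend. The trial is sized for its main comparisons only, so any test of effect modification starts with limited power. A split reduces it further and makes the answer depend on one unexplained cut point. A flat result from the two-group comparison could then be read as evidence that the effect does not vary with age when the comparison was simply weak.

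**Working it through.** The plan states no figure for the age subgroup, so there is none to reproduce. The check is how much information about a linear change of effect with age survives the split.

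**Inputs from the protocol article**
- Cut at 70 years (Sub-group analyses).
- Final sample: "The study aims to achieve a final sample of 635 patients from at least 42 practices" (Sample Size Calculation).
- Significance level: "Statistical significance will be taken at the 5% level for both primary and secondary outcomes" (Randomised controlled trial analysis). Sidedness is not stated; two-sided is assumed.

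**Assumptions, not in the article**
- The effect changes linearly with age.
- The shape of the age distribution and the share q of patients under 70, both varied below.
- Clustering by practice is ignored in the ratio of the two approaches.

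**Formula.** The share of information kept is the squared correlation between age and the indicator of being under 70.
- Normal age: φ(c)² / [q(1 − q)], where c is the standard normal quantile of q.
- Uniform age: 3q(1 − q).

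**Normal age**

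| Split at 70 | Calculation | Kept | Lost |
|---|---|---|---|
| 50:50 | 0.3989² / 0.25 = 2/π | 63.7% | 36.3% |
| 60:40 | 0.3863² / 0.24 | 62.2% | 37.8% |
| 70:30 | 0.3477² / 0.21 | 57.6% | 42.4% |
| 80:20 | 0.2800² / 0.16 | 49.0% | 51.0% |

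The normal formula is symmetric in q, and the median split is its best case, so 36.3% is the smallest loss wherever 70 falls. With an assumed mean of 62 to 70 years and SD of 8 to 11, the loss runs from 36.3% to 56.1%. Two truncated normal shapes give 36.7% (mean 67, SD 10, range 45–85) and 41.1% (mean 67, SD 12, range 45–80).

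**Flatter age distributions**
- Uniform on 50–90 (half under 70): 3 × 0.5 × 0.5 = 0.75 kept, 25.0% lost.
- Uniform on 50–85 (57% under 70): 26.6% lost.
- Beta(3,2) on 40–90 (48% under 70): 31.1% lost.
- Uniform with a 70:30 split: 3 × 0.7 × 0.3 = 0.63 kept, 37% lost. The 25% to 31% range therefore also needs 70 to fall near the middle.

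**What this means for a test.** Suppose, for illustration, that an interaction test with age in years had 80% power. After the split, power is Φ[(1.960 + 0.842) × √(share kept) − 1.960].
- Normal, median split: 2.802 × √0.637 − 1.960 = 0.276, so power is about 61%. The sample needed to restore 80% is 1/0.637 = 1.57 times as large.
- Uniform, median split: 2.802 × √0.75 − 1.960 = 0.466, so power is about 68%, and the multiple is 1/0.75 = 1.33.

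In patients, with the stated 635 analysed, the split tests a linear age trend about as well as 0.637 × 635 = 404 patients with age in years (normal, median split), 0.576 × 635 = 366 (normal, 70:30) or 0.75 × 635 = 476 (uniform, median split).

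**The case against.** The strongest reply is that nothing here is wrong or contradictory. The section is a short list of subgroup names in a condensed article, with no model or interaction test given for any of them. A continuous-age model may sit in an analysis plan that is not shown. If the only aim is to report the effect in patients under 70 and in older patients, the loss above does not apply to those two estimates. Naming one cut in advance is common practice, is easy to report, needs no assumption of linearity and guards against a cut chosen from the data. If the effect truly steps at 70, the positions reverse: by the same squared correlation, a linear-age interaction would then be the less efficient test.

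Much of this stands. It rules out two stronger readings that a reader might infer. One is that the split certainly discards more than a third of the age information. The article gives no age distribution and no shape for the trend, and flatter age shapes give 25% to 31%. The other is that the split has no benefit, which the advantages just listed refute.

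What does not fall is the narrower point. The cut is stated in the article, not left open. It comes without a reason, exact age is collected, and a gradual change with age would be tested more efficiently without the cut. The absence of a model in the article is not itself a fault and is not raised as one.

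**Conclusion.** The concern holds as a conditional point about efficiency. Testing effect modification by age through the split at 70 loses at least 36% of the information if age is roughly normal and the effect changes linearly with age. It loses about 25% to 31% if age is closer to uniform and 70 lies near the middle. Both the age distribution and the linear trend are assumptions.

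It is minor. A reader might infer that the trial's main findings are weakened; they are not. This is one of six subgroup analyses, none with stated power, and no primary outcome, sample size or decision rule rests on it. Nothing is lost for good either, because date of birth is collected and age in years can still be modelled.

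**What to change.** Add a sentence to the analysis section: effect modification by age will be tested by an arm-by-age interaction with age in years, in a model that allows for clustering by practice, with a quadratic age term and its interaction with arm as a check on shape. Report the estimated effect at two or three ages. Keep the prespecified under-70 and 70-or-over estimates for display.

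The cost is that sentence and no new data. The downsides are that the test assumes a shape for the age trend, which the quadratic term checks only in part, and that it is less efficient than the split if the effect truly steps near 70. If there is a reason to expect such a step, stating it would justify keeping the split as the test.

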**Methods:**

SPHERE is a cluster randomised controlled trial, with practice-level randomisation to intervention and control groups, recruiting 960 patients from 48 practices in three study centres (Belfast, Dublin and Galway). Primary outcomes are blood pressure, total cholesterol, physical and mental health status (SF-12) and hospital re-admissions.

The intervention takes place over two years and data is collected at baseline, one-year and two-year follow-up. Data is obtained from medical charts, consultations with practitioners, and patient postal questionnaires.

The SPHERE intervention involves the implementation of a structured systematic programme of care for patients with CHD attending general practice. It is a multi-faceted intervention that has been developed to respond to barriers and solutions to optimal secondary prevention identified in preliminary qualitative research with practitioners and patients. General practitioners and practice nurses attend training sessions in facilitating behaviour change and medication prescribing guidelines for secondary prevention of CHD. Patients are invited to attend regular four-monthly consultations over two years, during which targets and goals for secondary prevention are set and reviewed. The analysis will be strengthened by economic, policy and qualitative components.

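### Intention to treat is said to cover all randomised patients, yet no stated route brings in the 30% or more planned to lack two-year blood pressure, cholesterol or SF-12

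*Protocol article*

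**What the plan says.** In the protocol article, Data Analysis, under Sub-group analyses, the first analysis approach is "By intention to treat i.e. including all randomised patients, regardless of their participation in the intervention". Under Randomised controlled trial analysis the contrast is fixed: "The analysis examines intervention vs control groups on study completion, as opposed to looking at changes in the intervention and control groups from baseline".

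The Sample Size Calculation section opens with "The study aims to achieve a final sample of 635 patients from at least 42 practices". Its list of assumptions adds "A final completion rate of 70% is anticipated" and "Practice attrition of 12.5% has been allowed for"; the paragraph after that list uses 10% for practice attrition. The abstract gives the number entering as "recruiting 960 patients from 48 practices in three study centres".

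Under Data Collection, blood pressure and cholesterol come from a practice consultation, SF-12 from a postal questionnaire, and other items from a chart search. All three are repeated at baseline, one year and two years, and "Data are collected at one year to assess the initial effects of the intervention". The Background section gives the purpose of these time points as showing both early and lasting change. The sample size section also says that the final analysis will use more efficient modelling, without naming a model.

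**The concern.** The analysis statement promises every randomised patient. The stated comparison uses the end-of-study value, which about a third of patients are planned not to have. Nothing in the stated comparison uses the baseline or one-year value to represent those patients. Followed as written, it compares the patients seen at two years, under an intention-to-treat label.

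Whether that matters depends on who drops out. Only intervention patients are invited every four months to have goals reviewed (Intervention, Level 2), and in the Republic non-GMS patients pay for those visits (Economic Evaluation, Introduction). It is plausible, though not shown, that poorly controlled patients in that arm leave more often. The remaining intervention patients would then look better without any true effect.

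**Working it through.** **1. The plan's own figure.** Cholesterol drives the sample size (Power Calculations, Cholesterol).
- Design effect: 1 + (15 − 1) × 0.019 = 1.266 (stated 1.27).
- 500 × 1.27 = 635; 635 / 0.70 = 907.1 (stated 907). Rounding up to 48 practices × 20 patients gives 960.

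The chain reproduces from 500 onward, and it shows that the powered sample is the patients who finish. (The 500 itself lies between 482 and 518, the totals without and with continuity correction; the point does not depend on it.)

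**2. Planned loss from 960.**
- 70% completion alone: 960 × 0.70 = 672 left, 288 lost, 30.0%.
- Stated final sample: 635 left, 325 lost, 33.9%.
- 70% completion and 10% practice attrition compounded: 960 × 0.70 × 0.90 = 605 left, 37.0% lost.
- The same with 12.5%: 960 × 0.70 × 0.875 = 588 left, 372 lost, 38.8%.

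The plan divides patient numbers by 0.70 only, so the last two are upper readings.

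**3. How many a one-year value could bring in.** The split of loss between years is not stated. Taking the 288, the number with a one-year but no two-year value is 0 if all leave before one year, 144 if half leave in each year, and 288 if all leave in year two.

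**4. Scale for a proportion (cholesterol).** Planned rates of poor control are 0.36 × 0.8 = 28.8% in controls and 0.36 × 0.5 = 18.0% in the intervention arm, a difference of 10.8 points.
- Suppose that difference is seen among the observed fraction f. The difference in everyone is f × 10.8 + (1 − f) × x, where x is the control-minus-intervention difference among the unobserved. It reaches zero at x = −25.2 points for f = 0.70 and at x = −17.1 points for f = 0.6125.
- Extreme bounds with 30% missing in each arm: 0.70 × 10.8 ± 30 = −22.4 to +37.6 points.
- Illustration with no true effect: assume that only the intervention arm's drop-outs differ, with a rate of poor control 10, 20 or 30 points above that arm's completers. The spurious benefit is 0.30 × gap = 3, 6 or 9 points. With 336 / 1.27 = 265 effective patients per arm, the chance of a significant benefit is about 12%, 35% or 68%.

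**5. Scale for a continuous outcome.** Simulation with no true effect, 48 × 20 patients, ICC 0.011 (the blood pressure value), 12.5% practice loss and 1,500 trials per setting. Assumed, not in the document: correlation 0.55 between visits, loss split equally between years, and drop-out in the intervention arm depending on the last observed value with log-odds slope 0.2, 0.4 or 0.6 per SD (odds ratios about 1.2, 1.5 and 1.8).
- Patients observed at two years, unadjusted: bias 0.04, 0.07 and 0.11 SD in favour of intervention; type I error about 7%, 13% and 22–24% (two runs). On the stated SF-12 SD, 0.04 × 8.39 = 0.3 and 0.11 × 8.39 = 0.9 points.
- Same patients, adjusted for baseline: about 0.02 SD of bias left at the two larger slopes.
- Baseline and one-year values used for everyone with any follow-up (a sequential-regression estimator standing in for the mixed model): bias within 0.004 SD.
- Standard error: about 0.085 SD unadjusted, 0.066 SD with baseline and one-year values. Nearly all of this gain comes from baseline.
- Drop-out alike in both arms: no bias in the unadjusted comparison.

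**The case against.** The strongest reply is that nothing here is contradictory. The sentence on study completion names a time point and rejects change scores; it does not define an analysis set. The intention-to-treat sentence is mainly about patients who do not take part in the intervention. Missing-data rules are commonly left to a full protocol or analysis plan, which is not shown, and the promise of more efficient modelling leaves room for them. All of this stands. A reader might infer that the protocol prescribes a completers-only analysis, or that it discards the one-year data; the text says neither.

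The chart search can supply some outcomes without attendance. That is enough to take hospital re-admissions out of this point. It helps less for the others: blood pressure and cholesterol are listed as consultation measurements, the chart item on risk factors concerns whether they are recorded, and SF-12 cannot come from a chart.

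The mechanism is also assumed. Data are collected identically in both arms, and missing a four-monthly visit is not the same as missing the two-year measurement. The 70% is an allowance; the cited studies completed 68.7% and 93%. The largest simulated SF-12 bias, 0.9 points, is small beside the 5-point target. Drop-out was simulated to depend on observed values, so an estimator that assumes this is unbiased by construction. These points limit the size of the concern. They do not supply a route into the stated comparison for patients without a two-year value.

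**Conclusion.** The point holds in limited form. The article promises all randomised patients, states only an end-of-study comparison, and plans for 30% to 38.8% to lack the end-of-study value. For blood pressure, cholesterol and SF-12 the default, absent another rule, is therefore a comparison of patients observed at two years.

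The possible bias is 0.04 to 0.11 SD if drop-out depends on outcome in the intervention arm only, over the assumed range of slopes, and nil if drop-out is alike in both arms. The documents do not support the stronger conclusion that the result will be biased, because they give no evidence on how drop-out will depend on outcome. The case for changing the wording rests as much on precision (standard error about 0.085 down to 0.066 SD) and on honest labelling as on bias.

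**What to change.** In the Randomised controlled trial analysis and Sub-group analyses sections:
- Keep the arm difference at two years as the primary contrast. For blood pressure, cholesterol and SF-12 as continuous outcomes, estimate it with a mixed model that fits the one-year and two-year values jointly, with the baseline value, arm, visit and arm-by-visit as terms and random effects for practice and patient. Include every randomised patient with any follow-up value. The same model gives the one-year effect.
- If the proportions with poor control, on which the trial was powered, are analysed, use the matching binary model or multiple imputation from baseline and one-year values.
- Name the observed two-year comparison as a sensitivity analysis, and add one analysis that shifts the missing two-year values in the intervention arm.
- State that patients with no follow-up value are not in the model, so that all randomised patients is not claimed for these outcomes unless they are imputed.

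The cost is analysis wording only: all three waves are already collected in both arms, and Stata, already named, fits such models. The downside is that the model assumes drop-out depends on observed values, which is why the shift analysis is needed.
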